## Abstract

**Background:**

Spinal cord injury (SCI) is a severe neurological disorder resulting in loss of movement and altered sensation with lifelong impacts on health, function, and social integration. Multidisciplinary SCI rehabilitation primarily focuses on enhancing function and independence while simultaneously managing secondary health conditions and providing psychosocial support. Therefore, a major goal in SCI rehabilitation should be strengthening patients’ capacity to cope with and adjust to challenges they encounter. Using a mixed methods design, the primary aim of this study is to integrate psychosocial guidelines that promote psychological adjustment into SCI rehabilitation, and second, to evaluate facilitators and barriers to their successful implementation.

**Methods:**

To determine perceived depth of knowledge, beliefs, and attitudes about psychosocial care, and usage of psychosocial guidelines, healthcare professionals in the three specialist SCI services in New South Wales, Australia will be invited to complete a baseline survey. Following the survey, semi-structured one-to-one interviews and focus groups will be conducted with healthcare professionals representing different health disciplines to understand the context and generate ideas about how best to integrate these guidelines into clinical practice. Based on the surveys, interviews, and focus groups, an implementation intervention employing educational strategies, structural, and nudge (behavioural change) approaches will be designed and implemented over a period of 18-months to facilitate integration of the guidelines into the SCI services. A post-intervention survey with healthcare workers will then be conducted. Focus groups from each SCI service, with representation across the different healthcare professions, will also be conducted to identify facilitators and barriers to implementing the guidelines. Success of implementation will be determined by analyzing any shifts in perceived knowledge, attitudes, and behaviour of staff and cultural/structural processes observed through comparing baseline and post-intervention qualitative and quantitative data. To capture lived experience insight, 10 patients with SCI currently undergoing rehabilitation will be interviewed.

**Discussion:**

This study will establish the success of implementing psychosocial guidelines into three specialist SCI services. It is hypothesized that constructive changes will occur in the knowledge, attitudes, and behaviour of the SCI Unit healthcare professionals, leading to improved psychosocial practices and patient outcomes that will strengthen person-centred healthcare in SCI rehabilitation. This study has been retrospectively registered with the Australian New Zealand Clinical Trials Registry on the 7th of May 2024. The registration number is: ACTRN12624000581561

## Background

Spinal cord injury (SCI) is a severe injury to the spinal cord resulting from either a traumatic or non-traumatic cause that is associated with disability (1, 2). In the past, SCI has been more prevalent among males, particularly those aged 16–30 years of age due to a higher risk of traumatic injury, such as a road traffic crash or sporting injury (3). More recently, there has been a further demographic shift towards a bimodal age distribution whereby countries with ageing populations, like Europe, the USA and Australia, have seen an increase in the rate of SCI in older people, particularly females, aged 65 years and older sustaining a SCI following a fall (3, 4). Thus, we now see two distinct groups within the traumatic SCI population, those injured in early adulthood and those injured in older age. Additionally, non-traumatic, non-progressive spinal cord conditions can result from illness or disorders, such as spinal stenosis, transverse myelitis, epidural abscess, spinal cord ischemia, or hemorrhage (5).

SCI is often associated with substantial physical disability and likelihood of secondary health conditions, such as chronic pain, spasticity, autonomic dysreflexia, cardiovascular disease, pressure injuries, respiratory complications, and urinary and bowel problems (6). Psychological comorbidities including depressed mood and anxiety disorders, as well as catastrophizing styles of thinking are also prevalent in adults with SCI (7–9). Thus, alongside inpatient medical treatment and rehabilitation, accurate evaluation, diagnosis, and treatment of mental health conditions is important since psychological and emotional distress is common following SCI (7–9) and may contribute to these common secondary health conditions.

People with a SCI are at greater risk of developing mood and anxiety disorders, suicidal thoughts, and self-perceived stress compared with the general population (7–9). Yet secondary mental health conditions often go undiagnosed, particularly during the early stages post-injury when the primary focus is on improving the physical function of people with SCI. Psychological comorbidities are clinically relevant and require clinical attention as they can interfere with the intensive learning process involved in rehabilitation following SCI, especially when they go undiagnosed (2). For example, if depression is undiagnosed and left untreated, it may have a longer duration and become harder to treat over time (10, 11), In turn, secondary psychological comorbidities that go untreated may impede adjustment to the community following discharge from rehabilitation, potentially hindering return to work and social participation (2, 7, 9), and may lead to additional psychosocial disability for people living with SCI.

Cognitive impairment is another common co-occurring condition after a SCI (12–15), with a pre-morbid history or comorbid brain injury being a frequent contributor (12, 13, 15). In fact, it was recently found that the increased likelihood for an adult with SCI to have cognitive impairment was 18 times higher than for an able-bodied adult (16). Despite this, it is concerning that a brain injury, especially minor traumatic brain injury (mTBI), can often remain undiagnosed and thus untreated (17, 18). This can hinder the uptake of self-managed behaviour and the development of independent living skills (17–19), ultimately disrupting the overall process of rehabilitation and adjustment to SCI. Yet even in the absence of a concomitant mTBI, it is not uncommon for adults of all ages with a SCI to experience impairments in their cognitive functioning due to a range of factors like cardiac regulation problems, fatigue, psychological disorder, chronic pain, older age, sleep disorder, and neural inflammation (12–17, 19, 20). For example, fatigue has been found to be associated with delayed memory performance and experiencing pain can reduce attention capacity (20, 21). Additionally, recent research found that mental health issues such as elevated anxiety are linked to a decline in working memory (21). Considering that mental health conditions like anxiety can often be undetected during SCI rehabilitation, there exists an inherent risk of negative adjustment to the injury (2, 21). A further complication to the adjustment process is that up to 56% of people with a SCI have been found to meet the common criteria for polypharmacy, defined as at least five medications prescribed concomitantly, which can also be associated with cognitive impairment (22). More so polypharmacy is of particular concern for people with advancing age (23) due to the risk for delirium (24).

Employing a biopsychosocial model of care for SCI rehabilitation is key to delivery of person-centred care (2). This model encourages healthcare professionals to consider physiological, psychological, and social contributors to a person's health care experience (25, 26). In addition to guidelines that address the physical aspects of rehabilitation for individuals with SCI, the authors contend there is a need to integrate psychosocial guidelines into the rehabilitation process. Psychosocial guidelines aim to provide healthcare professionals with essential insights into how to communicate with, support, and engage/motivate patients with a newly acquired SCI during their rehabilitation, especially when cognitive impairment is present (2, 26). Such a holistic approach seeks to optimize person-centred care for these individuals. Healthcare professionals are in a unique position to provide not only physical health care, but also psychosocial health care to inpatients with a SCI in the first months after their injury. The value of integrating psychosocial care guidelines and employing patient-centred goals into the SCI rehabilitation setting will, arguably, positively influence how patients adjust to their injury (2, 26, 27). However, many healthcare professionals working in SCI acute care and rehabilitation settings often lack the necessary training to apply psychosocial care as part of standard practice for everyone (26). For example, healthcare professionals working in the acute and rehabilitation phases need to have the confidence to screen for symptoms of mild cognitive impairment and mental health comorbidities in their patients, and in response, have the confidence to integrate and adopt psychosocial care strategies to foster optimal coping and adjustment skills in their patients (26).

A Cochrane review suggested the uptake of clinical practice guidelines in areas such as cardiology and cancer care can be improved if implementation tools encourage the adoption, penetration, and sustainment of the guidelines into routine practice by healthcare professionals (28). In the USA, professional standards of practice have been developed for SCI rehabilitation staff (29), though we are unaware of any evidence about the success of the integration of these standards into practice. In the United Kingdom (UK), a psychological care pathway model and best practice guidelines are being developed, drawing upon guidelines being used by the National Spinal Injuries Centre Stoke Mandeville Clinical Psychology Service (30), however, again, there is no evidence yet available of the success of their integration into SCI services in the UK. Clinical practice guidelines for managing mental disorders after SCI have also been developed by the Paralyzed Veterans of America Consortium for Spinal Cord Medicine, yet no evidence is available for their implementation (31).

There is a growing body of research on various methods for supporting clinician decision-making to align more closely with using specific evidence-based practices (32), with distinct strategies that can be categorized as passive (such as posters) or active (such as workshops) (32, 33). A novel way to strengthen clinical practice in line with desired standards is the “nudge” paradigm for behaviour change (32, 34). The premise is that behaviour can be voluntarily shifted by making specific choices instinctively appealing (35). Furthermore, an enabling culture that supports clinicians to engage in the process of change is also recognized as important for successful integration of new standards of practice (36).

In Australia, a Psychosocial Guide was developed for healthcare staff working in SCI rehabilitation but was never thoroughly integrated into the SCI rehabilitation process (37). Consequently, in a strategy to integrate this Guide into practice more effectively, it was recently upgraded by researchers and representatives from the multidisciplinary team of healthcare professionals working in SCI rehabilitation, as well as a colleague with lived experience of SCI (38). During this developmental and consultation stage in which a substantial upgrade of the prior 2014 psychosocial guide designed for SCI rehabilitation was completed, evidence regarding relevant psychosocial practice guidelines was accumulated by conducting a series of literature reviews over a 6-month period using primary search terms such as “*spinal cord injury*”, “*rehabilitation*”, “*adjustment*”, “*treatment*”, used in combination with secondary search terms such as “*depression*”, “*pain*”, “*cognitive impairment*”, and “*social participation*” (39)*.* When the guide was updated, consultation occurred by subjecting these guidelines to review by a diverse range of expert healthcare professionals involved in the medical and psychosocial care in specialist SCI services in NSW, Australia. Consensus was also sought for a new section on cognitive impairment in patients with SCI participating in rehabilitation, designed to be inserted into these guidelines. This was eventually achieved by conducting a rigorous e-Delphi study with the provision of evidence-based statements. Participants in the e-Delphi study were all experts in SCI rehabilitation, including one member with lived experience of SCI. These cognitive impairment guidelines were integrated into the updated guide when consensus was reached. Thus, a major upgrade to the recent psychosocial guide were strategies for the psychosocial management of SCI patients with cognitive impairment. The updated Guide is now publicly available online (38, 39) and was developed to support multidisciplinary healthcare professionals to improve their person-centred care of patients with acute SCI.

### Aims and objectives

Recognizing the difficulties of integrating past versions of the Psychosocial Guide into SCI rehabilitation practice, the primary aim of the intervention is to implement and integrate the latest Guide (upgraded in July 2023) into the three specialist SCI services in NSW, Australia. To facilitate this, a mixed methods approach will be employed to develop a multi-dimensional implementation intervention based on systems thinking (e.g., players, processes, interactions, technology) and focussed behavioural change techniques. The implementation objectives involves the use of the Consolidated Framework for Implementation Research (CFIR) (40), providing an ideal structure with which to explore individual, team, and organizational (inner setting) and health system level (outer setting) barriers and facilitators to the implementation of the Guide. This will be achieved through interviews and focus groups with the multidisciplinary healthcare professionals in SCI services and individuals living with SCI, according to CFIR domains. Further to this, the implementation objectives are to increase awareness, knowledge, and understanding of the Psychosocial Guide, and to co-design a set of implementation strategies and embed a plan to promote sustainability of the intervention in the SCI services.

## Methods/design

### Settings

The study will be conducted in three specialist SCI services in NSW, Australia, with one facility mostly providing acute care, another only subacute rehabilitation and a third Unit providing both acute care and subacute rehabilitation. The three SCI services have variations in catchment areas, as well as infrastructure and organisation of professional teams, workflows, and processes for SCI rehabilitation.

### Participants

Healthcare professionals including nurses, physiotherapists, occupational therapists, speech pathologists, medical specialists, social workers, psychologists, and psychiatrists working in the three SCI services will be invited to participate in an online survey pre-and-post intervention that will determine their understanding and awareness of psychosocial SCI care principles and practices. A selection, based on expertise and availability, of these participants from the different disciplines (*n* = 15) will then be invited to attend one-on-one interviews that will inform a tailored set of strategies to support changing or strengthening clinician behaviours in adopting the evidence-based guidelines. After the intervention, a further selection of healthcare professionals will again be invited to participate in either an interview or a focus group (again depending on their availability) to determine facilitators and barriers to implementation. Inclusion criteria will consist of (a) healthcare professionals from each of the three SCI services located at three NSW hospitals who volunteer to participate in the study; (b) a minimum of 12-months work experience; (c) representation by all SCI disciplines, and (d) being able to communicate effectively in English. The researchers will invite key informants that meet the inclusion criteria to be interviewed to ensure we capture the views of a broad range of healthcare professionals.

Since the major aim of this project is to introduce the Guide for the first time to the three SCI services in NSW, in order to encourage adoption, penetration, and sustainment into practice, given the nature of this research we believe there is no value for using a control/comparison group in this project.

Additionally, up to 10 adults aged between 18 and 80 years with SCI, able to communicate effectively in English, who are currently undergoing rehabilitation, and not experiencing severe mental illness or at risk-behaviours will also be interviewed, to obtain their perceptions and awareness of psychosocial care during rehabilitation. Patients with SCI who meet the inclusion criteria will be invited to participate. They will be interviewed at one of the three sites in-person by a member of the research team.

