### Stage 3: Evaluation

Again, guided by the organizational (inner setting) and health system level (outer setting) of the CFIR model, mixed methods assessment consisting of quantitative (online surveys) and qualitative data (interviews and focus groups) will be employed to determine the effectiveness of the interventions conducted over the 18-month period. All multidisciplinary healthcare professionals working with patients with SCI will be invited to complete a follow-up (i.e., post-intervention) survey after the delivery of the interventions. Follow-up interviews with a small number of healthcare professionals (*n* = 15) and focus groups (*n* = 20) will help to evaluate the implementation. The follow-up interviews and focus groups will explore the personal experiences of healthcare professionals as well as changes at a systems level. As mentioned previously, a small number (*n* = 10) of patients with SCI who are undertaking inpatient rehabilitation within the SCI services will also be interviewed after implementation of the Guide. The study will evaluate the success of implementing the Psychosocial Guide within the three SCI services using an audit and feedback strategy. This will be achieved through developing indicators for best psychosocial practice standards in terms of guideline uptake and adherence, health professional perceived knowledge, attitudes and skills, reduced barriers to change, changes in unit culture, and norms priorities and processes. To gauge effectiveness and level of satisfaction of care from a patient viewpoint following the introduction of the new Psychosocial Guide, a set of indicators that measures the quality of psychosocial care for SCI rehabilitation will also be determined based on patient experiences, impacts, and satisfaction with care. The outcome will establish whether there is a case for the widespread adoption of the implementation intervention in NSW and Australian hospitals to promote the use of the Guide.

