## Discussion

Sustaining a SCI can have a devastating lifelong impact on daily functioning, participation, and quality of life (30). Additionally, rehabilitation following SCI involves an intensive inpatient period that can be overwhelming and distressing, which in general may be for between 3 and 6 months in Australian SCI services, depending on injury severity (7, 30). This protracted time in hospital will increase the risk of isolation and institutionalization (30). Following rehabilitation, patients are discharged into the community where less support is available than when in hospital, so emphasis should be on assisting people with SCI to adjust and cope (53). Arguably, therefore, implementing psychosocial guidelines in the rehabilitation phase is essential to improve delivery of person-centred care, providing a supportive environment in which the person with SCI will learn to develop autonomy within their individual level of functioning and begin the journey of adjustment and adaptation to their injury (30, 54).

To our knowledge, this is the first study that will assess the impact of implementing psychosocial guidelines into the inpatient SCI rehabilitation setting, as well as determining potential barriers and facilitators for implementation. In addition, our study is a multifaceted endeavour that addresses the holistic needs of both people with SCI and healthcare professionals. By advancing health literacy and enhancing the capacity of healthcare professionals, it is intended to strengthen the foundations for a more inclusive, informed, and supportive healthcare landscape. Thus, it is anticipated this study will improve the delivery of psychosocial care in the acute and rehabilitation phases of SCI and therefore, provide helpful guidance on strategies that will improve implementation of psychosocial care and establish whether there is a case for the adoption of such a multidimensional implementation intervention in other SCI services in Australia and worldwide.

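### An uncontrolled before-after evaluation in three services is said to determine effectiveness and settle whether wide adoption is justified; the conclusions should be limited to observed change

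*Protocol article*

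**What the plan says.** The protocol article has the following on this point.

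- **Comparator (Participants).** There is none: "given the nature of this research we believe there is no value for using a control/comparison group in this project". The reason is in the same sentence: "Since the major aim of this project is to introduce the Guide for the first time to the three SCI services in NSW", with the purpose of getting it adopted, spread and sustained in practice.
- **Basis for judging success (Abstract, Methods).** Shifts in staff knowledge, attitudes and behaviour and in unit processes are to be "observed through comparing baseline and post-intervention qualitative and quantitative data".
- **Effectiveness (Stage 3: Evaluation).** Surveys, interviews and focus groups "will be employed to determine the effectiveness of the interventions conducted over the 18-month period". The section also plans practice indicators and patient-experience indicators.
- **Adoption (Stage 3: Evaluation).** "The outcome will establish whether there is a case for the widespread adoption of the implementation intervention in NSW and Australian hospitals".
- **Adoption, wider (Discussion).** It is anticipated that the study will "establish whether there is a case for the adoption of such a multidimensional implementation intervention in other SCI services in Australia and worldwide".
- **Hypothesis (Abstract, Discussion).** Changes in staff are expected, "leading to improved psychosocial practices and patient outcomes that will strengthen person-centred healthcare in SCI rehabilitation".
- **Limitations (Discussion).** Social desirability bias, resistance to change and resource constraints are named, and long-term impact is placed out of scope. Neither the missing comparator nor background change is named.

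**The concern.** Determining effectiveness, and settling whether other hospitals should adopt the package, are causal and generalising conclusions. They need some estimate of what would have happened in these services over the same 18 months without the intervention. The design collects none. Whatever else changes in that time is credited to the intervention, and an adoption recommendation would rest on it.

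The reason given for having no comparator does not close this gap. That the Guide is new to the services explains why every service should receive it. It does not explain why a comparison would be uninformative.

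**Working it through.** There is no stated figure to reproduce. The survey size of 60 (Mode of assessment) rests on estimated staff numbers (Analyses), with no significance level, power or expected change. The check therefore sets the sections against each other.

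**1. What the design can estimate.** With one round before, one round after and every service exposed, the quantity observed for any outcome is

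observed change = intervention effect + background change + change in who responds + effect of being asked twice.

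This is one equation with four unknowns. Only the sum is estimated. More respondents make the sum more precise but do not divide it into its parts.

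**2. Whether the other terms could differ from zero here.**

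- *Background change.* The interval is 18 months (Stage 2: Implementation). The Guide can also be reached outside the intervention: "The updated Guide is now publicly available online" (Background).
- *Staff turnover.* Stage 2 and the Discussion plan for onboarding new staff. Eligibility requires 12 months of work experience (Participants). Even if that means experience in the unit, a person who joins in the first 18 − 12 = 6 months of the implementation period qualifies by its end. The survey is anonymous (Discussion), and no linkage of the two rounds is described.
- *Different patients.* Stage 1 and Stage 3 each describe interviews with 10 patients. The Discussion puts the usual inpatient stay at 3 to 6 months, far below 18, so two rounds would involve essentially different people.
- *Repeat survey.* Staff who answer both rounds have already met the questions. The items were written by the researchers and are not validated (Mode of assessment).

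**3. Outcome by outcome.** The Discussion expects staff to have no baseline knowledge of the Guide. For awareness of the Guide, the starting level is thus near zero and the rival explanations are weak, so a before-after rise is reasonably informative. Attitudes, culture, general psychosocial practice and patient satisfaction existed before the Guide and can move for other reasons. Stage 3 lists outcomes of this second kind among its evaluation targets.

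**4. Aim against conclusion.** Aims and objectives gives the primary aim as putting the Guide into practice, with barriers, facilitators, awareness and co-design as objectives. The Discussion says the main focus is to launch it. An uncontrolled design fits that aim. It does not fit the effectiveness and adoption sentences in Stage 3 and the Discussion, and nothing in the article withdraws them.

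**The case against.** The strongest reply is that this is an implementation study. Its primary aim is integration of the Guide, and for that aim leaving out a comparator is defensible. This stands, and it is why the point concerns the conclusions and not the conduct of the study. It does not rescue the sentences that claim effectiveness.

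Several stronger readings are tempting, and the document does not support them.

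- *A reader might infer that a two-point survey alone decides effectiveness.* Stage 3 describes a mixed-methods evaluation. Follow-up interviews and focus groups ask directly about the intervention's impact and can bring other service changes to light. They help with attribution, but they too have no comparator and do not measure background change.
- *A reader might infer that the article promises a favourable case for adoption.* Its wording leaves a negative answer open, and the worldwide statement is introduced as an anticipation. Even so, the design cannot be relied on for either answer.
- *A reader might infer that every outcome is equally uninterpretable.* Awareness of the Guide is an exception, as shown above.
- *A reader might want a false-positive rate under an assumed drift.* The Analyses section states descriptive statistics and an evaluation of change over time. No test, significance level, continuous score or linkage is given, so such a rate would describe assumptions and not this study.
- *A reader might infer that a staggered start is required.* The three services differ in type of care (mostly acute, subacute only, both; Settings), so a service not yet started would differ from the others in more than timing. Three services would not give a powered test, and extra survey rounds add to the repeat-survey effect.

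**Conclusion.** The point holds as a mismatch between design and stated conclusions. The evaluation can describe change over the implementation period, and barriers and facilitators. It cannot determine effectiveness for attitudes, culture, general practice or patient satisfaction, and it cannot by itself settle whether wide adoption is justified. The rationale for having no comparator is adequate for the implementation aim and inadequate for the effectiveness claim.

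The size cannot be put in numbers from the document. The conclusion does not depend on any assumed amount of drift; it requires only that background change, turnover and repeat-survey effects cannot be taken as zero over 18 months. The correction should be made, because it changes what the study may conclude. It does not stand in the way of data collection.

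**What to change.** All the required changes are wording.

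1. In Stage 3: Evaluation and the Discussion, replace the effectiveness claim with a description of observed change over the implementation period and of barriers and facilitators.
2. Replace both adoption sentences with: *the results will inform whether a controlled evaluation is warranted*.
3. In the Abstract's Discussion, limit the hypothesis in the same way, so that it does not run causally from staff change to patient outcomes.
4. In Participants, replace the reason for having no comparator with one based on the implementation aim and on feasibility (three services of different type, a small pool of staff).
5. In the Discussion, name the lack of a comparator as a limitation. Say which outcomes it affects most, and that awareness of the Guide is more interpretable.

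The cost is a less favourable stated conclusion; no data collection changes. Staggered starts with repeated surveys are optional and would show background change only roughly. Registration was retrospective, so the order of starts may no longer be open.
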